#### Ethical Considerations

Student participants will be given training and support through the project to ensure adequate research skills, mental health and addictions knowledge, and support regarding self-care, coping and stigma [69]. We will actively encourage students with lived experiences of mental health concerns and/or substance use to participate through our recruitment efforts. However, participants will not be asked to publicly disclose or discuss their mental health status at any point throughout the engagement activities. We will be engaging vulnerable individuals in this process, and protocols will be put in place to monitor and respond to participants’ needs at various stages in the study. Access to appropriate mental health crisis support will be identified for each university or college recruitment site, and information regarding services will be provided to all participants. Key members of the research team will be able to provide emergent clinical input or direction, should the need arise. These members of the research team will also provide direction and training to ensure appropriate, meaningful, and effective engagement with youth, especially vulnerable youth.

#### Analysis Plan

Data gathered during the various engagement activities will be thematically analyzed by qualified members of the research team and interested students. These data sets will be used to answer the research questions and inform Phase 2 of the project (ie, the RCT). We will use a thematic analysis process [70] to review the collected data, generate codes, develop themes, and present the findings in a final report. Collated notes and transcripts will be provided to students, to verify their accuracy and elicit feedback on the analysis.

A descriptive statistical analysis will be conducted on all sociodemographic responses. Acceptance and feasibility will be analyzed using the USE Questionnaire [68] *.* Means and standard deviations for each category of the questionnaire will be analyzed. The extent of participants reporting high, medium, or low levels of satisfaction on the USE Questionnaire will also be calculated.

Using the study results, we will identify specific enhancements to the Thought Spot platform. We anticipate enhancements will include (1) user analytics and feedback mechanisms, (2) peer mentorship and/or coaching functionality, (3) crowd-sourcing and data hygiene, and (4) integration of evidence-based consumer health and research information. Modifications will be made to the platform by QoC Health, with oversight provided by the TSSG and the research team. The modified platform will undergo usability testing at the UHN Centre for Global eHealth Innovation.

We will also use gender-based analyses of the data in both phases. Mental illness and substance use disorders develop and present in different ways, and at different rates, for young females and young males. For example, young females aged 15-24 years have higher rates of depression than their male counterparts (9% vs 5.3%); however, young males are more likely to suffer from substance use disorders than young females (4.7% vs 1.7%) [71]. Data regarding participants’ gender identities and orientations will be voluntarily and confidentially collected at intake. Results will be analyzed to assess similarities and differences between and among gender groups. This comparison will help us to identify unique help-seeking needs and patterns to better tailor the intervention, and ensure it is inclusive of all gender identities and sexual orientations.

### Phase 2: Randomized Controlled Trial

An RCT, with 2 arms, will be conducted in Phase 2 to assess the impact of Thought Spot on self-efficacy for mental health help-seeking and health literacy among our target population. Students in the intervention arm will have access to the Thought Spot platform (online and mobile versions), while the control arm will receive usual care (access to campus health services, Web- and print-based information materials). The study will last 6 months. Participants in the intervention arm will receive an in-person tutorial on how to use Thought Spot, as well as access to an online *tour the app* video. Data will be collected from participants through online questionnaires at baseline, 3 months, and 6 months. The full procedure regarding the design of the RCT and administration of the intervention will be codeveloped with students in Phase 1.

The main outcome measure will be changes in help-seeking intentions, measured by the General Help-Seeking Questionnaire (GHSQ), which will be administered at baseline, 3, and 6 months. This scale is composed of 10 items measured in a 7-point Likert scale that ranges from *Extremely Unlikely* to *Extremely Likely*. The items are sources of help (eg, parent, friend, family doctor) and the participants are asked their likelihood of seeking help from each source. The 10 items are usually split into *informal help sources*, *formal help sources*, and *I would not seek help from anyone*.

We will also use the Actual Help-Seeking Questionnaire (AHSQ) and Attitudes Toward Seeking Professional Psychological Help Scale-Short Form (ATSPPH-SF) to measure secondary outcomes: help-seeking behaviors and help-seeking attitudes. These scales are most often used in help-seeking studies [72], and have been used in similar studies and with similar populations, often together [13,22,73,74].

Adequate internal consistency has been reported for the GHSQ in studies of high school students aged 12-19 years (Cronbach alpha range of .70–.90) [75,76] and university students (Cronbach alpha=.67) [77], as well as adequate validity and very good test-retest reliability (*r*=.86) [75]. The correlation between intentions to seek mental health care for personal-emotional problems and actually seeking care has been found to be positive and significant for the GHSQ (*r* s[218])=.17, *P*<.05). The ATSPPH-SF has demonstrated good internal consistency (Cronbach alpha range of 0.82–0.84), 1-month test-retest reliability of 0.80, and a correlation of 0.87 with the longer ATSPPH scale, among samples of college students [78-80].

In addition to these scales, we also plan to explore self-reported changes in self-stigma using the Self-Stigma of Seeking Help Scale [81] and self-efficacy using the Youth Efficacy/Empowerment Scale - Mental Health [82]. We will also gather data on demographics and general mental health status (Global Appraisal of Individual Needs - Short Screener, Canadian/CAMH version) [83] to examine trends, comparisons, and correlations between the study groups.

#### Statistical Analyses

All analyses will be carried out using SAS System 9.4 for Windows. Statistical tests will be 2 sided, with confidence levels of 0.05. Prior to testing, a series of univariate analyses will be carried out to ensure that model assumptions are met. To address the primary study hypothesis, a mixed-effect model will be used to account for the longitudinal nature of the data, and for attrition. Missing values will be treated with maximum likelihood estimation in SAS PROC MIXED, which uses all available information in the data. Intention-to-treat analysis will be used; all patients will be analyzed as they were originally allocated after randomization. As a sensitivity analysis, the final model will be fitted only with subjects for whom there is complete data. Formal help-seeking score will be the dependent variable, with study groups (intervention and control) and time points as predictors, and relevant sociodemographics collected at baseline as covariates to control for possible confounding. The interaction between study group and time will be included in the model, and linear contrasts will be used to compare the groups, specifically regarding the change from baseline to the final time point. Similar models will be used to address the exploratory hypotheses, which examine different scales and trends, on the effect of the intervention over time. Bonferroni adjustment will be used to control the Type I error rate if multiple comparisons are desired. Generalized estimating equations will be used for the AHSQ, since this scale is binary.

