### Approach to Bias Control

We are using computer-generated random allocation of subjects to the intervention and control arms, by means of the Research Randomizer website [85]. This will be a partially blind study, in that the process of inviting students and collecting data will not be done by the researchers. Missing values will be minimized by sending reminders to participants at least 3 times, and the offer of an honorarium at the end of the fourth data collection point. It is possible that students in the control group may use Thought Spot, so we will ask control subjects at the end of the final survey whether they accessed Though Spot during the study. This approach will allow us to carry out a sensitivity analysis to exclude control subjects who accessed Thought Spot. To mitigate this possibility, we will investigate password protecting the platform or tracking email addresses through a sign-in process during the trial period. We cannot guarantee that control subjects will not interact with intervention subjects, causing some contamination, but given the personal nature of mental health conditions, we believe this risk will not be highly prevalent.

Certain members of the research team were involved in the development of the original Thought Spot platform. To avoid bias or perception of bias, the scientific lead for the project, who was not involved in the development of the original Thought Spot platform, will oversee the RCT.

### Hypotheses: Phase 2

We hypothesize that transition-aged youth who receive the intervention will show a greater improvement in intentions for, and self-efficacy in, help-seeking for mental health concerns, compared to those who are allocated to the control group (usual care; resource pamphlet). We also hypothesize that participants in the intervention arm will show greater improvements in health literacy, increased self-efficacy in managing their mental health concerns, and a reduction in mental health stigma, compared with the control arm.

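### As described, the primary model's baseline covariates barely adjust the change-from-baseline contrast they are meant to adjust; adding covariate-by-time terms is a cheap, minor improvement

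*Protocol article*

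**What the plan says.** The Statistical Analyses section of the protocol article describes the primary model term by term. "Formal help-seeking score will be the dependent variable, with study groups (intervention and control) and time points as predictors", and to these it adds "relevant sociodemographics collected at baseline as covariates to control for possible confounding". It then states: "The interaction between study group and time will be included in the model". The arms are to be compared by contrasts whose target is worded as follows: "specifically regarding the change from baseline to the final time point". No other interaction is mentioned. The article does not say outright that the covariates enter as main effects only.

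Two further statements in that section matter here. On missing data: "Missing values will be treated with maximum likelihood estimation in SAS PROC MIXED, which uses all available information in the data". As a sensitivity analysis, "the final model will be fitted only with subjects for whom there is complete data". The Power Analysis section assumes 40% attrition, and the Approach to Bias Control section states that allocation is random.

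**The concern.** Baseline is one of the outcome visits in this model, and the deciding quantity is a change from that baseline. A covariate measured once and entered without a time interaction shifts a student's baseline, 3-month and 6-month scores equally. It explains differences in level between students but says nothing about how far they change. The stated purpose of the covariates and the stated contrast therefore do not meet.

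Three things are at stake. The report could describe a sociodemographically adjusted effect that is nearly or exactly the unadjusted one. Precision available from covariates that predict change would go unused. And if students drop out in a pattern that depends on both arm and a covariate predicting change, the model would correct only part of the resulting bias.

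**Working it through.** **Inputs.** From the Power Analysis section: 236 per arm, effect 0.41 points, Cohen's d 0.25 (so SD = 0.41/0.25 = 1.64), within-subject correlation 0.6, attrition 40%. From the Phase 2 description: visits at baseline, 3 and 6 months. Covariate effects, imbalances and covariate-specific dropout rates are not in the article and are assumptions throughout. All fits below use maximum likelihood with unstructured covariance. The article gives no adjusted estimate to reproduce.

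**Algebra, complete data.** Write the score of student *i* at visit *t* as arm-by-time mean + βxᵢ + error. The change from baseline to month 6 is then

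Yᵢ₆ − Yᵢ₀ = (arm-specific change) + (βxᵢ − βxᵢ) + error,

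and β drops out. The contrast equals the raw difference in mean change. With a term γₜxᵢ instead, the change keeps (γ₆ − γ₀)xᵢ and is adjusted.

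**Numerical check, complete data.** True effect 0.41, binary covariate worth 0.5 points of change, shares 60% and 40% in the two arms. Mean estimates:
- no covariate: 0.529
- main effect: 0.529 (identical to the first in every run)
- covariate by time: 0.426

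The gap of about 0.10 is the imbalance times the effect, 0.20 × 0.5. That imbalance was chosen to show the mechanism. The SD of a chance imbalance in a 50:50 covariate is √(2 × 0.25/236) = 0.046, so a typical unadjusted shift is 0.046 × 0.5 = 0.023 points.

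**Precision.** The within-stratum variance of change is 2 × 1.64² × (1 − 0.6) = 2.152. A balanced binary covariate worth 0.82 points of change (0.5 SD) adds 0.82² × 0.25 = 0.168. Removing it multiplies the standard error by √(2.152/2.320) = 0.963. With 40% covariate-independent dropout, that is about 0.170 to 0.164. For a covariate worth 0.5 points the factor is √(2.152/2.2145) = 0.986, a gain of about 1.4%.

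**40% attrition, no exact cancellation.** Final-visit contrast, true effect 0.41, covariate worth 0.8 points of level:

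| Scenario | No covariate | Main effect | Covariate by time |
|---|---|---|---|
| Random dropout, 60% v 40% imbalance, covariate also predicts change (0.5) | 0.513 | 0.512 | 0.415 |
| Dropout 20%/60% in one arm, reversed in the other; level only | 0.511 | 0.434 | 0.435 |
| Same dropout; covariate also predicts change (0.5) | 0.626 | 0.539 | 0.416 |

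In the second row the main effect does everything the interaction does. In the third it removes 0.087 of a bias of 0.216.

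**A milder crossed pattern, no true effect.** Dropout by covariate level is 25%/55% in the intervention arm and 50%/30% in control, averaging 40% in each. The covariate's share among completers is 0.75/1.20 = 0.625 against 0.50/1.20 = 0.417. For a covariate worth 0.5 points of change, bias is 0.091 unadjusted, 0.079 with the main effect and 0.00 with covariate by time; rejection rates are 9.3%, 8.6% and 5.2%. For 0.82 points, bias is 0.147, 0.129 and 0.00; rejection rates are 14.3%, 12.2% and 5.0%.

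**An uncrossed pattern.** With dropout of 30%/40% and 40%/50%, completer shares are 0.7/1.3 = 0.538 and 0.6/1.1 = 0.545. For a covariate worth 0.5 points, bias is about 0.007 × 0.5 = 0.004 in absolute size.

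**The case against.** The strongest reply is that the article never says main effects only. It names arm by time because that term carries the hypothesis, and a condensed article may leave other terms to an analysis plan that is not shown. This stands as a limit: the point rests on the natural reading of a listed model. One clause would settle it if covariate-by-time terms are already intended.

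Three stronger readings are tempting, and the documents do not support them.

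- **The covariates do nothing in the primary analysis.** Exact cancellation needs complete data. The primary analysis uses all available records with 40% loss expected, and there the main effect has some influence.
- **Most attrition bias would remain.** This is so only for covariates that predict change, and only if dropout differs by covariate in a way that differs between arms. For a covariate affecting level alone, the main effect removes essentially all the bias. The crossed dropout rates behind the larger figures are assumed, and nothing in the article suggests them. The assumed covariate effects on change, 0.5 and 0.82 points, also exceed the planned treatment effect.
- **The trial result would be confounded.** The article says: "We are using computer-generated random allocation of subjects to the intervention and control arms". Baseline differences therefore arise by chance, and without differential dropout the unadjusted contrast is unbiased over randomisations.

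These arguments reduce the size of the problem. They do not make the described model deliver the adjustment it claims.

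**Conclusion.** The point holds as a minor one. If the covariates enter as main effects, the complete-data sensitivity analysis is unadjusted in all but name, and the primary analysis is adjusted only indirectly through incomplete records.

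The consequences are modest:
- Chance imbalance is left unadjusted, typically a few hundredths of a point.
- A standard-error gain of about 1% to 4% is forgone, for covariates worth 0.5 to 0.82 points of change.
- Protection is incomplete when dropout depends on both arm and a covariate that predicts change. The residual bias runs from near zero under uncrossed dropout to about 0.1 points (0.079 and 0.129 in the two crossed cases above), against a planned effect of 0.41.

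The complete-data identity is exact. The attrition figures depend on the assumed dropout pattern and covariate strength, and should be read as a range of possibilities, not as a forecast.

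**What to change.** In the Statistical Analyses section, state that each prespecified baseline covariate enters together with its interaction with time point, with time treated as categorical. Keep the same baseline-to-final contrast between arms. Apply the same rule to the similar models planned for the other scales, and carry it into the complete-data sensitivity analysis.

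With three visits this costs two degrees of freedom per single-parameter covariate, which is negligible with 472 students, and it needs no new data. There is one small price to acknowledge: if dropout is strongly crossed and a covariate affects level only, the interaction adds nothing and widens the standard error slightly (0.165 to 0.172 in the 20%/60% scenario).

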### Other Analyses

A sex- and gender-based analysis will be completed when analyzing data for Phases 1 and 2. An economic evaluation of the Thought Spot intervention compared to usual care will also be explored to determine the potential cost-effectiveness and financial implications of sustainable and widespread use of Thought Spot throughout Canadian postsecondary campuses. The evaluation will be conducted from the perspective of future potential Thought Spot funders (eg, other Canadian postsecondary institutions). The primary outcome to be assessed will be the change in helping-seeking intentions among the target population.

### Approach to Bias Control

We are using computer-generated random allocation of subjects to the intervention and control arms, by means of the Research Randomizer website [85]. This will be a partially blind study, in that the process of inviting students and collecting data will not be done by the researchers. Missing values will be minimized by sending reminders to participants at least 3 times, and the offer of an honorarium at the end of the fourth data collection point. It is possible that students in the control group may use Thought Spot, so we will ask control subjects at the end of the final survey whether they accessed Though Spot during the study. This approach will allow us to carry out a sensitivity analysis to exclude control subjects who accessed Thought Spot. To mitigate this possibility, we will investigate password protecting the platform or tracking email addresses through a sign-in process during the trial period. We cannot guarantee that control subjects will not interact with intervention subjects, causing some contamination, but given the personal nature of mental health conditions, we believe this risk will not be highly prevalent.

Certain members of the research team were involved in the development of the original Thought Spot platform. To avoid bias or perception of bias, the scientific lead for the project, who was not involved in the development of the original Thought Spot platform, will oversee the RCT.

### Hypotheses: Phase 2

We hypothesize that transition-aged youth who receive the intervention will show a greater improvement in intentions for, and self-efficacy in, help-seeking for mental health concerns, compared to those who are allocated to the control group (usual care; resource pamphlet). We also hypothesize that participants in the intervention arm will show greater improvements in health literacy, increased self-efficacy in managing their mental health concerns, and a reduction in mental health stigma, compared with the control arm.

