Additional functionality includes crowd-sourcing, an increasingly important data-gathering technique that allows users of a content-rich resource to submit revised and/or new information that, after vetting, is fed back into the resource [54]. Thus, Thought Spot users can add additional *spots*, allowing them to grow the platform and shape it according to their needs and interests (Figure 4). This built-in crowd-sourcing functionality also includes the ability for users to give a simple *thumbs up* or *thumbs down* rating to individual services, and to make comments about particular services (Figure 5). Finally, building on an idea that came from the winning entry from the *Hackathought* event, users can find *wellness walks* built into the map (Figure 6). These routes are intended to reinforce the overall wellness focus of Thought Spot by encouraging students to take healthy breaks from their studies and other activities, and to explore the city in which they are studying, and become more connected with its communities. A functional Web version of Thought Spot [55] and a mobile app (for iOS and Android) are readily available online via free download. These platforms have gone through a series of usability testing sessions with student participants, using the state-of-the-art facilities and expertise at the University Health Network (UHN) Centre for Global eHealth Innovation. The current state of the platform has been assessed at Technology Readiness Level 6 [56].

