### Optimization Process and Research Methodology

The current study to optimize the Thought Spot platform will be conducted in two distinct phases, which will aim to (1) optimize the Thought Spot Web and mHealth platform through youth engagement, and (2) evaluate the impact of Thought Spot on self-efficacy for mental health help-seeking and health literacy among university and college students through a randomized controlled trial (RCT).

Participants will be recruited across 3 participating postsecondary institutions in the GTA: University of Toronto, Ryerson University, and George Brown College, which have respective enrolments of 84,556, 38,000, and 31,187 students [57-59]. Recruitment strategies will include invitation letters on public university bulletin boards, health and technology academic department listservs, student groups, Residence Life staff, and social media (Twitter, Facebook, and Instagram). All participants will be required to sign a consent form prior to being recruited into either phase of the study. Once participants have provided informed consent, they will fill out a nonidentifiable demographics form. This demographic information will be used for comparison purposes, reporting findings, and preparing formal evaluation reports.

To take part in Phase 1 of the project, participants must be transition-aged youth (16-29 years) [60] of any gender who are currently enrolled in part-time or full-time studies at any Canadian postsecondary institution. To take part in Phase 2, participants must be transition-aged youth (16-29 years) [60] of any gender who are currently enrolled in part-time or full-time studies of one of the 3 participating postsecondary institutions. All participants must have functional competency in English. Phase 2 participants must also currently be seeking mental health support or have a self-identified need for mental health support, and must have access to digital devices compatible with the Thought Spot digital platform. Participants who self-identify as having been hospitalized within the last 3 months for a mental health or addictions concern will be excluded from both phases of the study.

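### The contamination sensitivity analysis drops self-reported Thought Spot users from the control arm only, so it no longer compares the randomised groups; use should be recorded in both arms and analysed as randomised

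*Protocol article*

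**What the plan says.** All of the following is in the protocol article.

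- **Primary analysis** (Statistical Analyses): "Intention-to-treat analysis will be used; all patients will be analyzed as they were originally allocated after randomization". The model is a mixed-effect model fitted by maximum likelihood to all available data. The contrast is the change in formal help-seeking score from baseline to the final time point.
- **How use is measured** (Approach to Bias Control): "we will ask control subjects at the end of the final survey whether they accessed Though Spot during the study". The section describes no such question for the intervention arm and none at an earlier survey.
- **What is done with the answer** (same section): "This approach will allow us to carry out a sensitivity analysis to exclude control subjects who accessed Thought Spot".
- **Access during the trial** (same section): "we will investigate password protecting the platform or tracking email addresses through a sign-in process during the trial period". Neither measure is committed to.
- **Expected extent** (same section): no rate is given. On contact between participants in the two arms, the authors say "we believe this risk will not be highly prevalent".
- **Attrition** (Power Analysis): 40%, from 236 to 142 participants per arm.

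**The concern.** Whether a control participant finds and uses the app is decided after randomisation, and it may depend on how inclined that person is to seek help, which is close to what the primary outcome measures. Taking these people out of the control arm while leaving their counterparts in the intervention arm compares a selected group with an unselected one. The result then mixes any effect of the platform with the selection.

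The role this analysis may come to play makes that matter. Control use dilutes the intention-to-treat contrast. If the primary result is weak or null, readers will look to the analysis without the contaminated controls to see what the effect would have been. A larger difference there could be dilution removed, selection added, or both, and the analysis cannot tell them apart.

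The measurement adds a second problem. Because the question comes at the end of the last survey, controls who have dropped out never answer it, yet their earlier scores contribute to the mixed model.

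**Working it through.** **Inputs from the protocol article.** Power Analysis gives d = 0.25, a mean change of 0.41 points, within-subject correlation 0.6, 236 per arm and 40% attrition. The implied SD is 0.41 / 0.25 = 1.64 points. The plan's attrition arithmetic reproduces: 236 × 0.6 = 141.6, stated as 142 per arm. The article gives no contamination rate and no figure for how users differ from non-users, so both are assumed below and shown as ranges.

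**1. Bias of the exclusion when the platform has no effect.** Let c be the share of controls who use the app, and delta the amount by which their change would exceed that of non-users. Set the mean change of all controls to 0, which is also the intervention mean. With m1 for users and m0 for non-users:

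- c × m1 + (1 − c) × m0 = 0 and m1 − m0 = delta, so m0 = −c × delta.
- After the exclusion the contrast is 0 − m0 = c × delta.

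The table gives the bias in SD units, with its share of the design effect of 0.25 in brackets.

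| c | delta = −0.25 SD | delta = 0 | delta = 0.25 SD | delta = 0.5 SD |
|---|---|---|---|---|
| 10% | −0.025 (−10%) | 0 | 0.025 (10%) | 0.05 (20%) |
| 20% | −0.05 (−20%) | 0 | 0.05 (20%) | 0.10 (40%) |
| 30% | −0.075 (−30%) | 0 | 0.075 (30%) | 0.15 (60%) |

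**2. The same bias expressed through a correlation.** Let r be the correlation between the propensity to use the app and the change that would occur without it. Let the fraction c with the highest propensity be the users. The SD of change is 1.64 × √(2 × (1 − 0.6)) = 1.467. The bias is r × 1.467 × φ(z) / (1 − c), where z cuts off the upper fraction c of the standard normal and φ is its density. At c = 20% and r = 0.2 this is 0.2 × 1.467 × 0.280 / 0.8 = 0.103 points, or 25% of 0.41.

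With 142 completers per arm before the exclusion, the standard error at c = 20% is 1.467 × √(1/142 + 1/(142 × 0.8)) = 0.185. The table gives the bias in points, then the two-sided rejection rate under no effect at nominal 5%.

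| c | r = 0 | r = 0.2 | r = 0.3 |
|---|---|---|---|
| 10% | 0; 5.0% | 0.057; 6.2% | 0.086; 7.7% |
| 20% | 0; 5.0% | 0.103; 8.6% | 0.154; 13.3% |
| 30% | 0; 5.0% | 0.146; 11.8% | 0.219; 20.7% |

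At r = −0.2 the sizes are those for r = 0.2 with a minus sign.

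**3. Missing use data.** 236 × 0.4 = 94.4, so about 94 controls would not be asked. Keeping them leaves unidentified users in the control arm. Dropping them adds a second selection in that arm only.

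**4. An estimate that keeps the randomised groups.** Divide the intention-to-treat contrast by the between-arm difference in the proportion using the platform. Suppose, for illustration, a true effect of 0.41, full uptake in the intervention arm and the full effect in control users. The intention-to-treat contrast is then 0.41 × (1 − c) = 0.369, 0.328 and 0.287 at c = 10%, 20% and 30%. Dividing by 1 − c returns 0.41 each time. Treating the difference in use as known, the standard error grows by 1 / (1 − c), that is by factors of 1.11, 1.25 and 1.43.

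**The case against.** **Only a sensitivity analysis is affected.** The primary estimate is intention-to-treat and keeps every control. A reader might infer that the trial handles contamination in its main result by dropping controls; Statistical Analyses rules that out. This limits the weight of the point but does not remove it.

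**The direction is not established.** A reader might infer that the exclusion must favour the intervention. The contrast is a change from baseline, so people who merely start with higher intentions need not change more. On a bounded 7-point scale, those starting high may even change less. The population is also narrowed by eligibility: "Phase 2 participants must also currently be seeking mental health support or have a self-identified need for mental health support". All of this stands. A favourable bias is the likelier case if control users are the more active help-seekers, but nothing in the article proves it. Some of any rise over intention-to-treat would also be genuine removal of dilution.

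**The app may not be open during the trial.** The statement that the web version and "mobile app (for iOS and Android) are readily available online via free download" describes the platform as it stood before Phase 2. A reader might infer that it stays freely downloadable throughout; the article does not say so. What stands is that restriction is only to be investigated.

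**The question comes with the final outcome.** Anyone who supplies the final score can also be asked about use, so the gap of about 40% mainly concerns dropouts' earlier data in the mixed model. That is correct and is how the point is put here.

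**Prior users and Phase 1 participants.** A reader might want them excluded. Randomisation balances them in expectation, and the article leaves full trial procedures to be developed in Phase 1, so this is not part of the point.

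**Complier-average analysis has assumptions of its own.** It needs allocation to act on the outcome only through platform use, and the intervention arm also receives a tutorial. This stands, and is why those assumptions must be written down.

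**Conclusion.** The point holds, limited to the sensitivity analysis and its data collection. An exclusion made after randomisation, in one arm, on self-reported behaviour does not compare the randomised groups. It is biased whenever use is related to change in help-seeking intentions.

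With no true effect the bias is c × delta. At an assumed 20% use and 0.5 SD difference it is 0.10 SD, or 40% of the effect the trial is designed to detect. Over the ranges tabulated it runs from −0.075 to 0.15 SD, and it is zero if use and change are unrelated. These sizes rest wholly on assumed c, delta and r, because the article gives none of them. The intention-to-treat result does not carry this bias. The change is worth making before enrolment, but the primary analysis does not depend on it.

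**What to change.** 1. Replace the control-only exclusion, or accompany it, with a complier-average causal effect analysis that uses randomisation as the instrument for platform use and keeps everyone as allocated. State its assumptions and define what counts as use. If the exclusion is kept, label it as a non-randomised comparison.
2. Record use in both arms from the sign-in process already contemplated, and add a question on use at each follow-up survey. Use up to the last completed survey is then also known for participants who drop out later.
3. Settle the trial-period sign-in or access restriction before enrolment, rather than leaving it as something to investigate.

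**Cost.** Some additional analysis work, one question per follow-up survey, a wider confidence interval for the complier estimate than for intention-to-treat, and temporary restriction of open access to the platform. The sample size and the primary analysis do not change.
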